## Abstract

**Background:**

A high percentage of epithelial ovarian cancers (EOC) express the estrogen receptor (ER), which is an ideal target for endocrine therapy. Letrozole is a proven, potent aromatase inhibitor, extensively tested and used in the treatment of ER positive breast cancer. In addition, it seems a potent drug for patients with heavily pre-treated OC as demonstrated in several distinctive settings. However, it has never been evaluated prospectively in a maintenance setting for ovarian cancer after standard of care. The here proposed trial aims to define a population of EOC patients, who would benefit from the effectiveness of the generic agent letrozole, with little expected toxicity and thus beneficial impact on overall quality of life (QoL).

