**Discussion:**

The here proposed randomized phase III trial aims to identify patients with EOC in the maintenance setting, who benefit from the effectiveness of the letrozole, by proving its efficacy whilst maintaining a high standard of QoL due to the limited toxicity expected in comparison to the current alternative drugs on the market for this treatment phase.

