### Aims

There is a need to evaluate endocrine therapy in a prospective large phase III trial including and focusing on QoL aspects. We present a phase III randomized double-blind placebo-controlled multi-center trial that will assess the effect of the aromatase inhibitor letrozole as maintenance therapy in patients with FIGO Stage II-IV low and high-grade ovarian cancer of endometrioid or serous histotype. This experimental arm will be compared to the current standard, namely use of no maintenance endocrine therapy after the end of adjuvant chemotherapy, whereas, combined treatment with the new approved treatment options in this phase is allowed and has been proven safe [32, 33].

Based on the evidence presented above, we hypothesize that the letrozole maintenance arm will lead to a prolongation of PFS in these patients with no decrease of QoL. PFS has been selected based on previous data from our own study [28] and a recent meta-analysis [34] demonstrating a high potential benefit in regards to prolongation of the time to first relapse by 8 months using endocrine treatment in the maintenance setting.

Moreover, this study aims to identify the population that would benefit the most from this endocrine therapy in respect to prolonged quality of life (QoL). QoL will be assessed, prior, during, and after the intervention period, by both validated QoL questionnaires as well as by activity measurements. In addition, the survival status will be evaluated in relation to fragility and vulnerability as well. To this end, the G8 score will be used to assess fragility by patients over 75 years of age and the CD-RISC-10 score to assess resilience in the whole cohort.

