### Primary analysis

A Cox proportional hazards regression model will be implemented to study whether treatment influences PFS. In this model, we will stratify by grade of cell differentiation (HGOC or LGOC). The proportional hazards assumption will be checked by inspecting the scaled Schoenfeld residuals and formally tested by performing the Grambsch-Therneau test. No matter whether a violation of proportional hazards is detected, the hazard ratio (HR) with its 95% confidence interval will be presented as well as the p-value for that HR. If there is an indication of a non-proportional hazard rates, the restricted mean survival time (and its difference between arms) at t* = 5 years, and its confidence interval will be reported since they provide a more insightful statistic in such cases (following the recommendations of Royston and Mahesh [47]) Furthermore, Kaplan–Meier curves will be plotted by treatment arm.

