### Subgroup analysis

We will explore the impact of the experimental treatment vs the control in the following subgroups:- Bevacizumab treatment.- PARP inhibitor treatment.- Residual disease.- Grade (LGOC/HGOC).- Weak and strong ER expression.- Resilience categories/scores.- The elderly population (≥ 75 years).

For each subgroup, the primary analysis will be repeated. No other subgroups or subgroup analyses are pre-specified.

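### Subgroup effects are assessed only by repeating the primary Cox model within each subgroup, with no treatment-by-factor contrast named

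*Protocol article*

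**What the plan says.** The Subgroup analysis section opens with "We will explore the impact of the experimental treatment vs the control in the following subgroups". It then names seven factors: bevacizumab treatment, PARP inhibitor treatment, residual disease, grade, weak versus strong ER expression, resilience, and age 75 or over. The method follows in one sentence, "For each subgroup, the primary analysis will be repeated", and the next sentence ends the plan: "No other subgroups or subgroup analyses are pre-specified".

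The analysis to be repeated is defined under Primary analysis. It is a Cox model for the effect of treatment on progression-free survival (PFS), stratified by grade, with the HR, its 95% confidence interval and its p-value. It has no treatment-by-factor term, and the article mentions no interaction or heterogeneity test elsewhere.

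The article also speaks of finding who benefits. The abstract's Background says the trial "aims to define a population of EOC patients, who would benefit from the effectiveness of the generic agent letrozole" and its Discussion uses similar words. The Aims section says "this study aims to identify the population that would benefit the most from this endocrine therapy", and that sentence goes on to tie the aim to quality of life.

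**The concern.** Whether one group of patients benefits more than another is a question about a difference between two effects. A significant result in one level of a factor and a non-significant result in the other does not answer it, because the smaller level has fewer events and so less power even when the effect is identical. With seven factors and a p-value in each level, contrasts of the kind 'works here, not there' are likely even if letrozole works equally well in everyone. Such a contrast could lead readers to withhold the drug from, or restrict it to, a group on no real evidence.

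This is not a detail left open for the statistical analysis plan. The article states the method and says that nothing else is pre-specified.

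**Working it through.** **Inputs from the article** (Sample size considerations of the whole cohort; Randomization): HR 0.70, two-sided alpha 5%, 90% power, 330 events, 1:1 allocation. **Assumptions:** two levels per factor; shares of events of 10-50% in the smaller level, since the article gives no shares; every level judged at two-sided 5%.

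**1. The plan's own figure.** Events = 4(1.960 + 1.282)² / (ln 0.70)² = 330.4. The stated 330 events reproduce, with 90% power.

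**2. Power within a level when the HR is 0.70 in everyone.** With d events in the level, power = Φ(0.3567·√d / 2 − 1.96). For a 50/50 split, d = 165: Φ(2.291 − 1.96) = 0.63.

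**3. Chance that exactly one level is significant.** The levels contain different patients, so this is p₁(1 − p₂) + p₂(1 − p₁). For 50/50: 2 × 0.63 × 0.37 = 0.47.

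| Split of events | Events | Power in each level | Exactly one significant |
|---|---|---|---|
| 50/50 | 165 / 165 | 63% / 63% | 47% |
| 30/70 | 99 / 231 | 43% / 77% | 54% |
| 20/80 | 66 / 264 | 31% / 83% | 63% |
| 10/90 | 33 / 297 | 18% / 87% | 74% |

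**4. Seven factors on the same 330 events.** This was simulated with 6,000 trials per setting. Each event contributes a normal term with mean ln(HR) and variance 4. Four sets of shares between 10% and 50% were used, with factors independent or correlated (latent correlation 0.5). A contrast is counted when exactly one level shows significant benefit.

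- True HR 0.70 everywhere: at least one false contrast in about 82-96% of trials, on average about 3.2-3.9 of the seven factors.
- True HR 1.0 everywhere: about 16-18% of trials.

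**5. One interaction test per factor instead.** The false-positive rate is 5% per factor whatever the overall HR. Over seven independent tests, 1 − 0.95⁷ = 30%; the simulation gives about 25-30%. The expected number of false contrasts is 7 × 0.05 = 0.35.

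**6. What an interaction test can detect.** The standard error of the log ratio of HRs is √(4/d₁ + 4/d₂). At 50/50 it is √(8/165) = 0.220, so 80% power needs a ratio of exp(−(1.960 + 0.842) × 0.220) = 0.54. At 30/70, 20/80 and 10/90 the ratios are 0.51, 0.46 and 0.36. For a ratio of 0.70, power is 37% at 50/50 and 16% at 10/90.

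**The case against.** The strongest reply is that the subgroup work is labelled exploratory and that the article contains no rule declaring benefit wherever p < 0.05 and denying it elsewhere. On that view the figures above measure a reader's mistake and not a planned inference. This stands in part: it lowers the weight of the point. It does not remove it, because the only inferential output planned per subgroup is the one that invites the mistake.

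Several stronger readings are tempting but not supported.

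- *That the method cannot estimate a difference in effect.* Each subgroup yields an HR with its interval, and the levels of a factor are separate patients, so a ratio of HRs can be derived from the reported results. The gap is that no contrast is named or reported.
- *That the trial cannot answer its aim.* The sentence under Aims concerns quality of life, which a PFS interaction would not settle either. The abstract can be read as establishing benefit in ER-positive disease as a whole.
- *That, with no drug effect, 14 tests give a 51% chance of a false positive* (1 − 0.95¹⁴). The same patients enter every factor, so the tests are not independent; simulation gives about 34-35% in either direction. The article also does not clearly plan 14 tests: it lists the elderly as one group and allows resilience as a score.
- *That bevacizumab and PARP inhibitor groups will be formed from use after randomization.* The article does not say when they are classified, and the eligibility note on concurrent maintenance treatment fits status at entry.

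The low-grade cohort is a partial exception. It has its own group sequential design with an O'Brien-Fleming boundary, so the 5% threshold assumed above does not apply to it at the whole-cohort analysis. That design tests the effect within low grade, not a difference from high grade.

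Finally, interaction tests here have little power. That is true, and it is a reason to show the ratio with its interval, which makes the uncertainty visible.

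**Conclusion.** The point holds as a recommendation to improve a stated method. The article fixes separate within-subgroup analyses, names no treatment-by-factor contrast and closes the list.

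Under the trial's own design effect, a false contrast in at least one of seven factors is very likely (about 82-96%), against at most about 30% with one interaction test per factor. The size depends on the true effect: with no effect of letrozole it is about 18%. It also rests on assumed subgroup shares and two levels per factor, but the conclusion is the same across the range examined. The primary analysis is not affected.

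**What to change.** For each listed factor, fit the grade-stratified Cox model on all patients with treatment, factor and treatment-by-factor terms. For grade, include only the interaction, since the strata already absorb its main effect. Report the ratio of HRs with its 95% CI and the interaction p-value beside the subgroup HRs. Then state that:

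- within-subgroup p-values are not used to claim differential benefit;
- power for interaction is limited (80% power needs a ratio of HRs near 0.54 at a 50/50 split, and a more extreme one for unequal splits);
- with seven tests at 5%, about a 30% chance of at least one false interaction remains.

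As a safeguard, define the bevacizumab and PARP inhibitor subgroups by status at randomization, so that each remains a randomized comparison.

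The cost is a few sentences and one extra model per factor, written before unblinding. Sample size, primary analysis, the group sequential design of the low-grade cohort and patient care stay as they are.

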### Data management system and administration

The clinical trial data will be collected pseudonymized in an electronic data capture system, named secuTrial®. The secuTrial® database runs on a server maintained by the IT-Department of the University Hospital Basel. It is implemented (set-up and adjusted) by the data management group at the Clinical Trial Unit at the University Hospital Basel. Data management at the Clinical Trial Unit of the University Hospital of Basel will be performed as to their standard operating procedures, see CDMA Planning (2.0.1), CDMA Development, Testing and Release (2.0.1), CDMA Training (1.0.1), CDMA Locking and Closure (1.1.0) (SOPs CRO). Each study site is responsible for data entry into the secuTrial® database system.

In addition, the confirmed low-grade ovarian cancer data will be stored pseudonymized in the LOW-REG database created explicitly for the analysis of this sub cohort.

### Archiving and data retention

The secuTrial® database will be locked after all data has been monitored and all raised queries have been solved. Data will be exported and transferred to the Clinical Trial Unit University Hospital Basel according to internally defined processes (SOP’s CRO). Data will be archived by the Sponsor, except for the data and histological specimens of the subpopulation of low-grade ovarian cancers which are dispersed to the AGO (Germany).

### Monitoring

A monitoring team from the CRO will contact and visit all sites, either remote or physically, on initiation, during the study, and regularly if necessary. The Study Monitor will verify the adherence to the protocol and the completeness, consistence, and accuracy of the data being entered in the eCRF, to verify that the study is being conducted according to the protocol and within the specified period and the facilities and staff are adequately and trained, according to Risk Based Monitoring as described in the monitoring plan.

The Study Monitor will require access to all patient medical records including laboratory test results and surgery, pathology and radiology reports and supporting documents to verify the entries on the eCRF. The investigator (or his/her designee) should work with the Study Monitor to ensure that any problems detected during these visits are resolved and ensure that source data and documents are made accessible to the Study Monitor and answer questions by the Study Monitor.

### Participant`s confidentiality

The investigator will ensure that patient’s anonymity will be maintained during, as well as after the study (publication) and that their identities are protected from unauthorized parties. In eCRFs or additional trial documentation, patients will not be identified by their names, but by a unique identification code. The investigator must maintain documents with the patient’s identity at site hidden from the Sponsor in the ISF (e.g. patients written consent form in strict confidence at the site).

Direct access to source documents will be permitted for purposes of monitoring, audits and inspections. Monitors, auditors and inspectors will also maintain confidentiality of personal data of patients.

### Storage of biological material and related health data

The coded paraffin block from the central blinded pathology review and ER measurements (and the paraffin block provided after recurrence, if available) will be stored in the study biobank in the Histopathology Core Facility, Department of Biomedicine, University of Basel as described in the Swiss GO Trial Group biobank regulations. The paraffin blocks will be stored there for up to 20 years after the closing of this trial. Distinct written informed consent must be signed by each study participant for the analysis as well as the storage of these tumor tissues.

## Discussion

Despite optimized treatment for epithelial ovarian cancer the prognosis is poor with a maximum reported 5-year overall survival rate of up to 50% [1]. At present, the standard of care after a maximal surgical cytoreduction effort followed by adjuvant chemotherapy with carboplatin/paclitaxel is limited with maintenance therapy with bevacizumab for FIGO stages III-IV and additionally PARP inhibitor for HGOC with a BRCA mutation and partial or complete response to carboplatin/paclitaxel. Therefore, additional treatment options, particularly maintenance therapy regimens that might prolong this period of response are needed [48]. Nevertheless, some patients might be cured from the disease by the primary treatment already, so it is important that this treatment should be as tolerable as possible. A high percentage of epithelial ovarian cancer expresses ER, which is an ideal predictive marker for endocrine therapy response [49].

Letrozole is a potent aromatase inhibitor extensively tested and used in ER positive breast cancer patients and has also been tested in several smaller series for patients with heavily pre-treated epithelial ovarian cancer [29]. Letrozole in general is well tolerated and has been commonly used in breast cancer patients for more than 20 years. It has a preferable toxicity profile. Approximately 30% of patients have some mild symptoms like arthralgia, vaginal dryness and hot flushes. Recently, the combined use of Letrozole and Bevacizumab and Olaparib, respectively, has proven to be safe, as all toxicity observed was attributed solely to the new compounds and not to the letrozole [32, 33].

So far, it has not been prospectively evaluated in the adjuvant maintenance setting for ovarian cancer primary treatment. The MATAO trial aims to fill this gap and will evaluate for the first time prospectively the benefit of letrozole versus placebo in the maintenance setting of ER positive ovarian cancer.

Whilst long established in breast cancer, the highly effective option of aromatase inhibitors as adjuvant maintenance treatment has never been thoroughly examined for its use in ovarian cancer due to the disinterest of pharmacological industries. If this proposed trial would not be performed, in the near future every patient will be treated with drugs like PARP-inhibitors or bevacizumab as these will be the only drugs examined and approved for treatment in the maintenance setting of ovarian cancer [1, 4–6, 8, 9]. The toxicity profile of these drugs however, will not allow these to be applicable for all patients suffering from ovarian cancer, potentially excluding a large group of frail and vulnerable patients, the median age of onset being 63 years.

The proposed trial aims to create an opportunity for patients, who might benefit from the effectiveness of the generic agent Letrozole with proven efficacy and limited toxicity, with limited impact on their QoL whilst increasing their chance on prolonged PFS and ultimately on OS.

## Data Availability

The datasets that will be used and/or analyzed during the current study are not yet available as the study is presently ongoing, but will be available from the corresponding author in consultation with the national trial coordinators on reasonable request once recruitment and data collection are complete.

## Abbreviations

AACCI: Age Adjusted Charlson Comorbidity Index
ADAMON: Project to evaluate risk-adapted monitoring strategies for clinical trials
AE: Adverse Event
AESI: Adverse Event of Special Interest
AGO: Arbeitsgemeinschaft für Gynäkologische Onkologie/Working group Gynecologic Oncology
AI: Aromatase Inhibitor
ASCO: American Society of Clinical Oncology
AUC: Area under the curve
BASEC: Business Administration System for Ethical Committees
BRCA: Tumor suppressor gene for breast cancer
CA: Competent Authority (e.g. Swissmedic)
CA-125: Cancer Antigen 125
CDMA: Clinical Data Management Application
CEC: Competent Ethics Committee
CMO: Clinical Manufacturing Organization
CRA: Clinical Research Associate
CRF: Case Report Form
CRO: Contract Research Organization
CTCAE: Common Terminology Criteria for Adverse Events
CT: Computer Tomography
DSMB: Ata Safety Monitoring Board
ECOG status: Performance scale of Eastern Cooperative Oncology Group
eCRF: Electronic Case Report Form
EIG121: Estrogen-induced gene 121
EMA: European Medicines Agency
ENGOT: European Network for Gynecological Oncological Trial Groups
EOC: Epithelial ovarian cancer
EQ-5D-5L: European Quality of Life Scale, 5-Dimensions
ER: Estrogen Receptor
ESGO: European Society of Gynecological Oncology
FIGO: Fédération Internationale de Gynécologie et d'Obstétrique Gynécologie
FACT-ES: Functional Assessment of Cancer Therapy—Endocrine subscale
FACT-O: Functional Assessment of Cancer Therapy – Ovarian cancer symptoms subscale
GCIG: Gynecological Cancer Intergroup
GCP: Good Clinical Practice
hCG: Humane Chorion Gonadotropin
HGOC: High Grade (serous) Ovarian Cancer
HR: Hazard Ratio
HRA: Federal Act on Research involving Human Beings (in German: HFG, in French: LRH, in Italian: LRUm)
ICF: Informed consent form
ICON7: International Collaborative Ovarian Neoplasm (ICON) 7 trial
IHC: Immunohistochemistry
ITT: Intention To Treat
LGOC: Low Grade (serous) Ovarian Cancer
LOGOS: Histopathological identified subgroup of patients with low-grade ovarian cancer
MATAO: Trial for maintenance therapy with aromatase inhibitor in epithelial ovarian cancer
MICD: Minimum Important Clinical Difference
OFS: Ovarian Function Suppression
OS: Overall Survival
ORR: Overall Response Rate
PARP: Poly(ADP-Ribose)-Polymerase 1
PARPi: Poly(ADP-Ribose)-Polymerase 1 inhibitor
PFS: Progression Free Survival
PD: Progressive Disease
PI: Principal Investigator
PR: Progesterone Receptor
PRO: Patient Reported Outcome
p-value: Value for probability
QoL: Health related Quality of life
QAPFS: Quality-adjusted Progression Free Survival
Q-TWiST: Quality-adjusted Time Without Symptoms and Toxicity
RCT: Randomized Clinical Trials
RECIST: Response Evaluation Criteria in Solid Tumors
RFS: Relapse Free Survival
RNA: Ribo Nucleic Acid
SAE: Serious Adverse Event
SCBR: Summary Clinical Benefit Rate
SOP: Standard Operating Procedure
TFST: Time to First Subsequent Treatment
WHO: World Health Organization
